## Method and analysis

### GIAF toolkit

The impact analysis of the EMPOWER platform in three countries will use qualitative and quantitative analysis using the novel GIAF methodology.^20^ The GIAF methodology involves a framework and toolkit to assess the three main phases of implementation research (Initiation, Early Implementation or Maturity and Late Implementation or Evolution).^20^ For the EMPOWER study, the first two phases of implementation will be evaluated. The relevant GIAF tools are described below.

#### GIAF glossary of terms

The GIAF glossary of terms was developed and refined through a consensus-based approach with the collaboration and validation by an international panel of experts in implementation research and health policy to generate a common language for communication across different disciplines, research areas and countries. Prior development of glossaries of terms used the same approach in health services and systems research^23^ and in the analysis of healthy habits and longevity.^24^ The GIAF glossary provides a standard definition of 180 terms relevant to implementation and impact analysis and the GIAF methodology. Excerpts of the GIAF glossary and the definitions of the terms relevant to this study are provided in online supplemental appendix 1. They include the first two phases of implementation (initiation and maturity), the three main domains of Initiation (planning, pre-engagement and prereadiness), and the five domains of maturity (readiness, usability, dissemination, adoption and uptake).

#### GIAF taxonomy

The hierarchical taxonomy of the process of impact analysis in implementation research is shown in figure 1. This is an ontology-based classification system that follows two main rules: <part of>which defines parent and child categories in the hierarchical tree and <is a> or operational and mutually exclusive definitions included in the glossary of terms. It represents the three main domains of Initiation and the five main domains of maturity as well as their 53 subdomains or child categories. For example, ‘adoption’ is divided into seven subdomains (no adoption, awareness, incorporation, conversion, allocation, provision and routinisation) (refer to the definitions in online supplemental appendix 1).

**Figure 1 F1:**
[figure not shown]
The two phases and domains of the GIAF impact analysis methodology for the EMPOWER platform (the process of Initiation and Maturity (Early implementation)). EMPOWER, European Platform to Promote Well-being and Health in the Workplace; GIAF, Global Impact Analytics Framework.

#### Measurement and the GIAF checklists

One of the challenges of impact analysis is how to harmonise measurement of different domains that are categorical, ordinal or numerical and that can be adapted to the conditions of highly heterogeneous programmes and projects, requiring different coding and rating approaches. To overcome these challenges, we have developed three rating and representation systems of the results of the GIAF checklists: scales, ladders and profiles. For example, in the case of maturity or early implementation, only the domain ‘uptake’ follows a defined ordinal ranking (figure 1 taxonomy). Readiness, dissemination and adoption follow a quasi-ordinal ranking. These categories are typically labelled in a way that suggests an ordinal progression, but the degree of difference between the categories cannot be clearly defined. In addition, a step represented by one item in the checklist can be skipped or merged with the next step in a particular study. We call this ranking approach a ‘ladder’ defined as a measurement of the process in implementation that provides sequential levels which assign a qualitative gradient/meaning to complex entities which are not scalable. The difference between the levels of a ladder is not necessarily of equal or sequential value and does not imply a gradual progression across levels. In the real world, a ladder level can be skipped in a specific context, whereas in a rating scale, this is not possible.

For every domain, regardless of whether it is a scale, ladder or profile, there is a recommended rating technique using a checklist. A checklist is a collection of the nominal items which are directly linked to each level of the domain. Most of the GIAF checklists are based on prior standardised instruments. The planning checklist is an adaptation of several planning templates.^16 25^ We have adapted the Technology Readiness Level version of the Horizon programme at the European Union for the prereadiness domain (onitiation phase) and readiness domain (maturity phase)^26^ and assessed its feasibility and inter-rater reliability in a separate study.^27^ The usability checklist has been validated in previous studies.^17 26 28^ The dissemination checklist was iteratively developed but based on the WHO International Classification of Health Interventions categories of target, action and means,^29^ and the uptake scale has been adapted from.^30^ Finally, the adoption impact ladder was developed by our group and validated.^17 31 32^ It is preferable that the rating for each domain is identified by more than one researcher (two or more raters), and there is agreement across the researchers and stakeholders in every study. Peer-reviewed publications on the GIAF toolkit, validation studies and its uses in the real world are ongoing.^17 27 28 33^ Refer to the GIAF University of Canberra website for further details.^20^ Each checklist is ~10 pages long and consists of a glossary of terms, instructions for the rater, and each level contains the characteristics of that level, a description and examples, and level completion criteria. Table 1 shows an example of level (i) of the GIAF Planning checklist.

**Table 1 T1:** Level (i) of the GIAF Planning checklist

Level	Name	Characteristics	Description and examples	Level completion criteriaVerifiable information tick whether you deem the level is completed then document the information used to make your decision (documents, data, sources, opportunistic information). If there is not enough information to make a decision whether the criteria have been met for a level, please note this in the space provided.
i	Logic for change	Logic for change is a schematic representation which explains how the programme is intended to work, the process including the relationship between actions/activities and outcomes.Logic models are based on the understanding of how change happens.They are an explanatory account of how and why programmes give rise to outcomes.	A logic model is a tool used in programme planning and evaluation. It outlines a sequence of inputs (resources), activities (processes), outputs (results). It focuses on describing the logical flow of a programme without providing detailed explanations of the causal mechanisms.They can be created using different techniques and formats, such as flow charts, maps, tables, narrative or programme on a page. 	The logic for change is expressed in some form.Criteria Met? [figure not shown]
				Please document/comment below the information used to make your decision and note if there are any gaps in the logic model.

GIAF, Global Impact Analytics Framework.

### European Platform to Promote Well-being and Health in the Workplace

The EMPOWER app, available for use by employees, comprises four components:

Screening for psychosocial working conditions (eg, symptomology, work functioning) and screening for physical health, mental health and absenteeism.Recommendations to reduce psychosocial stress at work.Promotion of workplace mental health and well-being for example, psychoeducation, tools to reduce stress, promotion of healthy lifestyles and increase well-being.Modules to reduce absenteeism and presenteeism including psychoeducation and problem-solving.

The screening tool, the Psychosocial Stressors at Work Scale (PSWS), is a 16-item measure of psychosocial working conditions such as work overload, conflicts at work, burn-out, bullying and harassment. The results of the PSWS are then matched with recommendations for employees based on their level of stress.

The EMPOWER website contains an employer portal which provides summarised feedback to employers on the mental health of employees and recommendations for employers to address employee work-related stress and mental health issues.

### Implementation sites and target audience

The EMPOWER platform will be implemented in small-medium enterprises and public companies from a variety of sectors in three cities and regions in Europe: Barcelona (Catalonia, Spain), Turku (Finland), Lodz (Poland). Three European countries were selected to represent different European welfare and health service models: Finland (represents the Scandinavian model), Spain (Mediterranean model), Poland (Eastern European model). Two target audiences will be considered: (1) the employees from the participating companies (primary target of the EMPOWER project) and (2) the employers of these companies (secondary target).

All employees from the selected companies meeting the criteria will be invited to participate in the cluster RCT. The inclusion criteria for participants are: (1) being aged 18 years or older; (2) having a mobile phone with Internet access; (3) having sufficient knowledge of the local language and (4) giving informed consent. Once these criteria are met, participants will be invited to download and use the app. After obtaining informed consent, employees will be asked to complete several questionnaires and will then be guided through different modules and content sections of the EMPOWER app.^22^ All employee participants will answer a total of three assessments via survey through the EMPOWER app. This allows for separate analyses at the country and company levels and the level of the EMPOWER cluster RCT.

Companies will be selected based on being a SME or public agency (<250 employees). The country coordinators will approach companies who meet the inclusion criteria, provide information about the study and the EMPOWER platform and invite them to participate. Those who consent will enter into a contract between the researchers and employers to affirm ethical considerations, data collection and communications. Each workplace (and thus the employees) will be randomised into the RCT.

### Unit of analysis

The units of analysis are the key domains of the process of implementation throughout the two phases (Initiation, Maturity) (figure 1). In the Initiation phase, analysis will be at project level only (across the three countries). In the maturity phase, there will be an analysis of the impact of the implementation of the EMPOWER project, subgroup analysis at the country level (Finland, Poland and Spain) and some domains at the level of the recruited organisation/workplace.

### Training and preparation for data collection

The preparation for the data collection commenced prior to finalisation of the EMPOWER app development and commencement of the RCT. The country coordinators are researchers from universities in each country and members of the EMPOWER consortium. They are located in each country (Finland, Poland and Spain) and have attended training. Their tasks include monitoring and managing the trial fieldwork in their country, data entry and validation, solving problems during the fieldwork and will remain in constant communication with other EMPOWER consortium partners. For the impact analysis data collection, there were three orientation/training sessions with the country coordinators. In October 2021, an introduction to the impact analysis and explanation of the GIAF framework was conducted online for country coordinators and included an orientation on the dissemination run sheet (a spreadsheet with predetermined categories), used to collect data for the dissemination domain (maturity phase). The run-sheet enables concurrent collection (rather than retrospectively) of the parameters of dissemination activities (eg, the communication frequency with an employer). Country coordinators enter data on the activities to recruit organisations/workplaces and to make the EMPOWER platform known and make it used. An additional training session was held in April 2022 with regards to the dissemination run sheet, and a third meeting in September 2022 on the usability and adoption questionnaires to be used at the end of the recruitment period. The usability and adoption questionnaires (for employers) are conducted through a semistructured interview with the employer representatives. In preparation for the data collection on the usability, the questionnaire was first refined to the three country contexts in English. Each country coordinator translated the questions into their country language (all being fluent speakers of the language). There was subsequent collaboration with each of the country coordinators to culturally adapt the questions, yet ensure they remained within the integrity of the intent of the questions. Finally, each country coordinator translated the usability questions into the relevant language. Support to understand and use the GIAF tools to collect information relevant for the dissemination, usability and adoption domains will be provided to country coordinators as needed.

### Data collection methods

The GIAF methodology uses an approach involving checklists and which use diverse methods of data collection and from multiple sources including end users (employees of companies), employers, country coordinators and other consortium groups (eg, development and implementation groups) involved in reporting development progress and dissemination plans and activities. For each domain in the initiation and maturity phase, the data collection will be via a combination of the following sources of information (table 2).

**Table 2 T2:** GIAF data collection methods and sources

GIAF phase	Domains	Data collection
Initiation	PlanningPre-engagementPrereadiness	EMPOWER consortium documents (project proposal, consortium reports) with descriptors to extract specific information.
		Records of opportunistic information known to the Impact analysis researchers through working with EMPOWER consortium partners and country coordinators throughout the project, via direct observation, face-to-face, phone or email discussions or purposeful approaches to individuals, for example, country coordinators.
		Project progress reports, deliverable documents, consortium publications, meeting minutes and other documents with respect to development of the EMPOWER project and platform testing, prior to implementation
Maturity	Usability	End users—standardised surveys from the GIAF toolkit to collect information.
	Dissemination	Country coordinators—The GIAF toolkit dissemination spreadsheet with predetermined dissemination activity categories and definitions for each country coordinator to concurrently record dissemination activities.
	UsabilityAdoption	Employer representatives—Standardised questions by the country coordinators via a semi-structured interviews and/or survey with key workplace personnel.
	Uptake	EMPOWER website and app usage data from users (employees and employers as a secondary target audience).
Other	Contextual information–barriers and facilitators	Country coordinators—an interview on completion of the recruitment for the EMPOWER app regarding country-level barriers and facilitators.

EMPOWER, European Platform to Promote Well-being and Health in the Workplace; GIAF, Global Impact Analytics Framework.

The users (employees) of the app will be asked questions for the usability domain (maturity phase) via the survey platform Qualtrics. The three country translations of the usability questions will be uploaded to Qualtrics for distribution via email using a dedicated link to each user in the workplace. The questions will be sent to employees at 6–8 weeks after the completion of their 7-week use of the EMPOWER intervention. If there is no response after 3 weeks, a reminder will be sent at 4 weeks. Each usability question will be rated on a 7-point Likert scale ranging from 1=strongly disagree to 7=strongly agree. After each question, there will be a space for a free text comment.

The employers/their representatives will be invited to answer the usability domain questionnaire via an interview with the country coordinators up to 2 months after recruitment and the EMPOWER app use has ceased at that workplace. The timing depends on the progress of recruitment at the time. There will be slightly different wording for the usability questions to the employer, because of their context and level of knowledge (eg, budget, available resources). Employer responses will be rated on the same 7-point Likert scale (strongly disagree to strongly agree).

As the bilingual country coordinators are part of the EMPOWER consortium, they will ask the employers the adoption domain questions at the same time as the usability questions. Answers will be recorded on the paper-based questionnaire as free text. Survey and interview responses and dissemination spreadsheets were written by the country coordinators in English which was then provided to the University of Canberra impact analysis team.

The name of the workplace (not the representative’s name) and position of the responder in the company (eg, employer, employed manager, supervisor, work health and safety representative) will be made known to the University of Canberra team. The name of the workplace is necessary so the number of employees in each workplace is known, and uptake (the uptake by employees) of the intervention (EMPOWER platform) can be calculated.

### Organisational learnings

Organisational learnings (formative and summative) are a process in which an organisation’s members actively use the knowledge acquired during the project to guide behaviour in such a way to promote the ongoing adaptation and improvement of the organisation.^34^,^36^ In this context, organisational learning refers to learnings for the EMPOWER consortium about the EMPOWER intervention and its development and implementation, arising from the Impact Analysis. We will use all information gained from each of the initiation and maturity domains from each country and synthesise it to generate new insights across the three countries which have the potential to inform and improve future mental health e-health interventions and implementation processes at the workplace. We aim to describe the impacts of the EMPOWER project and provide insights into what worked, in what context and why.

Formative organisational learning will be collected throughout the initiation phase and the preparation of annual reports, related meetings, reports and general communications. The summative organisational learnings will be validated through two processes. First, the targeted feedback on country-level barriers and facilitators that will be collected by University of Canberra from each country team (Finland, Poland and Spain) via a semistructured interview. Existing implementation frameworks have been used to develop the focus questions for the semistructured interview.^11 16 37 38^ Second, two expert panels (consortium partners and country representatives) will generate the summative organisational learnings and validate them through consensus in conjunction with other consortium partners. For example, employee and employer feedback that will be obtained through the realist evaluation performed by the Erasmus team; the information from the stakeholder survey conducted by the Fondazione IRCCS Istiututo Neurologico Carlo Besta (paper under review); stakeholder focus groups and scoping review,^10^ and the results of the impact analysis will be used to compare and affirm key organisational learnings from all consortium partners and stakeholders.

### Analysis

The approach to the analysis translates the narrative and the qualitative information to quantitative data within the GIAF framework for further analysis. The analysis will use mixed methods from the qualitative data gathered to rate on standardised ladders, profiles and scales in the GIAF toolkit. Four researchers from the University of Canberra team will rate the project independently on the various domains.

A case study of the EMPOWER platform intervention will be developed, containing all information necessary for raters to rate each GIAF domain and will contain references to the relevant information sources. Each rater will document on each checklist, the evidence (derived from the data collected relevant to that domain) for their determination of the rating level. Means will be calculated from employee and employer usability scores and mapped to the usability checklist and scored. Uptake will be calculated based on the number of employees at each company/country divided by the number of EMPOWER users as a percent and mapped onto the checklist and scored. Adoption responses will be mapped onto the adoption checklist and scored. Dissemination will be rated using the relevant checklist and given a score using the ladder. Engagement will be scored based on information from the various meeting notes and reports.

If differences occur between raters in the level on the ladder/scale/profile, the ratings will be discussed among the University of Canberra team until a consensus is reached for the final rating of the project on each domain. The degree of agreement across raters will be provided in addition to the final ratings.

Statistical analysis will include descriptive statistics (mean, percent) as well as the analysis of the relationships between domains (variables) and the comparison of the usability of the tool evaluated by the various participant groups after the completion of the RCT (randomised controlled trial). The analysis will include non-parametric tests (correlations and median comparisons) where relevant. Both qualitative and quantitative approaches will also inform key learnings. For example, quantitative data from the usability questions will be compared with qualitative adoption responses and quantitative uptake calculations. This will provide important information such as the extent to which employees in each country considered EMPOWER useful, relevant and of value. This measurement of usefulness may positively influence the degree that EMPOWER is adopted and the extent of the uptake into the target audiences. Country level barriers and facilitators (from country coordinator interviews and information from the realist evaluation (employee and employer feedback) will provide context for high or low ratings.

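### The protocol's uptake formula is upside down: it divides employees by users, so the percentage falls as real uptake rises

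*Protocol article*

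**What the plan says.** The only uptake formula in the protocol article is in the Analysis section: "Uptake will be calculated based on the number of employees at each company/country divided by the number of EMPOWER users as a percent". The resulting figure is then taken "as a percent and mapped onto the checklist and scored".

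Four other places bear on how it should be read:

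- Data collection methods explains that the workplace name is needed "so the number of employees in each workplace is known, and uptake (the uptake by employees) of the intervention (EMPOWER platform) can be calculated".
- The same section identifies the app's users with the employees: "The users (employees) of the app will be asked questions for the usability domain".
- Table 2, in that section, gives the data source for uptake as "EMPOWER website and app usage data from users (employees and employers as a secondary target audience".
- Measurement and the GIAF checklists says of the maturity phase that "only the domain ‘uptake’ follows a defined ordinal ranking".

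Analysis also gives uptake a use beyond its own rating: "quantitative data from the usability questions will be compared with qualitative adoption responses and quantitative uptake calculations". It plans non-parametric correlations and median comparisons where relevant.

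**The concern.** Uptake by employees is ordinarily the share of employees who used the product, so headcount is the denominator. The article puts headcount in the numerator. The number this produces measures employees per user, which moves in the opposite direction to uptake.

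Direction matters here. Uptake is one of the five maturity domains, and the article singles it out as the one with a defined order. The second research question asks whether the framework can support a comparison across three countries, and Unit of analysis plans country-level results, with some domains at workplace level. A reversed percentage would present the least-used sites as having the largest figure, and would turn a positive association between usability and uptake into a negative one. Sites with no users, which are the plainest failures of implementation, would have no value at all.

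**Working it through.** **Inputs.** The formula and its use come from Analysis. The article reports no uptake value, so there is no figure of its own to reproduce. The headcounts and user counts below are assumptions; all headcounts are under the 250-employee limit given in Implementation sites and target audience.

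**Formulas.** Let E be the number of employees and U the number of users.

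- As stated: 100 × E / U
- Terms swapped: 100 × U / E

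**Step 1: users are employees of the company (U ≤ E).**

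| Company | E | U | As stated | Terms swapped |
|---|---|---|---|---|
| A | 200 | 10 | 200/10 = 2000% | 10/200 = 5% |
| B | 200 | 50 | 200/50 = 400% | 50/200 = 25% |
| C | 200 | 100 | 200/100 = 200% | 100/200 = 50% |
| D | 40 | 30 | 40/30 = 133% | 30/40 = 75% |
| E | 200 | 0 | undefined | 0/200 = 0% |

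Because U ≤ E, the ratio E/U cannot be below 1, so the stated figure is never under 100%. It reaches 100% only when every employee is a user.

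**Step 2: employer users are counted too.** Suppose M employer users, who are not in the headcount, are added to the users. The stated figure becomes 100 × E / (U + M), which is below 100% only if M exceeds E − U, that is, near full uptake.

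- E = 100, U = 99, M = 2: 100/101 = 99.0%
- E = 10, U = 9, M = 2: 10/11 = 90.9%
- E = 100, U = 20, M = 2: 100/22 = 454.5%

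The floor of 100% therefore depends on who counts as a user. The inversion does not.

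**Step 3: ordering and correlation.** Within a company, the stated figure is a constant divided by the swapped one. That is a strictly decreasing function for U > 0. Among companies A to D, the ranks from lowest to highest are 1, 2, 3, 4 with the terms swapped and 4, 3, 2, 1 as stated. In general a rank r among n companies becomes n + 1 − r, so a rank correlation of the raw percentage with another variable keeps its size and changes sign, provided the same companies, each with at least one user, enter both calculations. Countries are reversed in the same way if the country figure is formed from total employees and total users.

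**Step 4: consistency with the rest of the article.** Data collection methods needs the headcount in order to express uptake by employees, which points to headcount as the denominator. Analysis suggests that perceived usefulness may increase uptake, so the measure has to rise with use. The stated ratio fits neither, and no other sentence gives it the right way round.

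**The case against.** The best defence is that this is a slip of wording. The intended proportion can be recovered from Data collection methods and from the later part of Analysis. A value such as 2000% would be hard to miss for four raters who must document their evidence and settle differences by consensus. A silent reversal of published results is therefore unlikely. That lowers the likely harm, but it does not correct the text, which remains the article's only definition of the measure.

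The defence does succeed against three stronger conclusions that a reader might draw:

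- *Every uptake figure must be at least 100%.* This needs users to be a subset of the employees counted. Table 2 also lists employers in the usage data, so values a little below 100% are possible near full uptake.
- *Low-uptake companies and countries will receive the highest uptake rating.* The percentage is converted to a checklist level, and the cut-offs are not in the article. If the bands end at 100%, inverted values might fail to map, or might all land in the top level. Either would leave no usable ranking, rather than a reversed one.
- *Every correlation with uptake reverses exactly.* Analysis does not name the coefficient, or say whether the raw percentage or the checklist score is correlated. After mapping, ties can break the symmetry. If companies with no users drop out, the two calculations also rest on different sets of companies.

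It is also fair to say that uptake is one of eight domains in a largely descriptive impact analysis. Nothing in the article makes the trial's effectiveness comparison depend on it.

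**Conclusion.** The point stands: as written, the uptake formula has its terms reversed and conflicts with the article's own account of what uptake is for. It should be corrected before uptake is calculated or rated.

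The size of the error grows as uptake falls: in the assumed 200-employee company, a true 50% appears as 200% and a true 5% as 2000%. These values assume that users are employees of the company. The reversal of order and of the sign of rank correlations applies to the raw percentage among companies with at least one user. What happens to the checklist score cannot be settled from the article.

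The intent is probably the usual proportion, so this is an error in the stated definition and not evidence that results will be reported backwards.

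**What to change.** Replace the sentence in Analysis with a definition along these lines: uptake is the number of employees who used EMPOWER, divided by the number of employees at the company, times 100; for a country, both counts are taken over its participating companies.

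Two additions go beyond swapping the terms, because the article leaves them open:

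- State that a company with no users has an uptake of 0% and stays in the analysis.
- Report the employer use listed in Table 2 separately, not in this numerator, so that the result lies between 0% and 100%.

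The cost is one or two sentences of wording. The headcounts and usage data are already to be collected, so no new data are needed.
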